### Data collection and management

Researchers will ensure that participants’ anonymity is protected and the data collected will remain confidential so that their identities and any type of identifying information are protected. Two copies of the Informed Consent Form will be provided, and signed by the participants, researchers and guardians.

After signing the consent form, the participant may terminate their participation in the study at any time if they wish, without any consequences. The results of this study may be presented at meetings or publications; however, the identity of participants will not be revealed.

The data generated and analyzed in this study will be made publicly available in the repository of dissertations and theses of the Federal University of Rio Grande do Norte. The repository chosen follows open access guidelines, ensuring transparency and replicability of the results. In addition, the data will be presented in the form of a scientific article, which will be submitted to a specialized journal, with the aim of reaching a wider audience and contributing to the advancement of knowledge in the area.

### Management of losses or withdrawals

Losses will be carefully recorded, ensuring the reliability of the study. If any participant withdraws from the study, they will be removed from the sample. A logbook will be used to record information relevant to the study.

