### Selection criteria

Person of both sexes, aged 18 or over; be a student in the sixth semester of the UFRN Nursing course. Students in the sixth semester who have already attended other degrees, *stricto sensu* or *lato sensu* postgraduate courses, extension courses, free courses, short duration courses, or events that address the topic of leadership and absentees will be excluded from the study.

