### Allocation

To ensure random allocation into groups, simple randomization will be applied using the website www.random.org. This tool will perform the randomization completely randomly, without researcher interference, ensuring that all participants have an equal chance of being assigned to either the control group or the experimental group.

Although the participants self-selected when they enrolled, randomization was carried out after the enrolments were collected, with the aim of ensuring that everyone had the same chance of being allocated to the different experimental groups.

Participants in the control group will attend a conventional expository class, held in person at the Nursing Department. The class, conducted by the researcher, will last four hours in the afternoon and cover the same topics as those addressed in the online educational module. Both the experimental group, which will have access to the online module, and the control group, which will have access to the conventional class, will last 30 hours. The control group will attend a lecture given by the researcher, covering the same topics and in the same depth as the online module at the Nursing Department at the Federal University of Rio Grande do Norte, lasting four hours. Although the in person class will last four hours, the total workload for the control group will also be 30 hours, as there will be suggested supplementary reading to be consumed.

Meanwhile, participants in the experimental group will engage in an online educational module, with recorded classes hosted on the Google Classroom virtual learning environment. Participants will have a period of five days to access and consume the module’s content, totaling 30 hours, from registration to completion. After the class, all the participants in the research, both the control group and the experimental group, will be called to go in person to the Nursing Department of the Federal University of Rio Grande do Norte to complete the post-test and receive certification of participation in the course.

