### Intervention

The sample will consist of approximately 40 students from the sixth semester of the Nursing course who are regularly enrolled. Throughout their participation, both online and in person, the participants will use exclusively their own mobile devices and internet access for registration and the pre-test.

The pre-test will be administered via Google Forms, and no prior support materials will be provided. Participants will have 20 minutes to complete the pre-test, which will be conducted by the researcher using a Google Meet room as the virtual space to accommodate all participants, as everyone needs to answer the pre-test synchronously within the estimated 20 minutes. The virtual tool’s chat feature will be used to signal completion. All participants must respond within the allocated time.

Randomization will be conducted only with participants who complete the pre-test and meet the eligibility criteria. These students will be randomly assigned to either the Control Group or the Experimental Group. After randomization, participants will be informed via WhatsApp and email about which group they belong to: those attending the in-person course at the Nursing Department or those consuming the online educational module.

Participants in the Experimental Group will be enrolled in a Google Classroom course by the researcher, with instructions sent via email and WhatsApp. The online educational module, consisting of interactive recorded classes, will have a duration of four hours, with additional content such as digital materials, quizzes, and forums. Topics covered include team motivation and engagement, organizational culture, conflict management, and constructive feedback. Participants will have flexibility in accessing the classes and will not be restricted by geographical location.

The Control Group will attend a conventional expository class held in person at the Nursing Department of the Federal University of Rio Grande do Norte. The class will use visual materials, such as PowerPoint presentations, covering the same topics as the online module with equal depth and breadth.

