Although the online modality and conventional teaching is the central focus of this study, it is important to consider that the conditions of each approach involve differences beyond the form of content delivery. In the online module, participants will have access to video classes, e-books, podcasts, videos available on a streaming platform (Youtube), quizzes and a forum for discussion, promoting greater flexibility and autonomy in learning. The in person course, on the other hand, will offer direct interaction with the instructor through a conventional lecture with the use of a visual resource using Powerpoint.

These variables should be taken into account when analyzing future results, as they reflect specific aspects of each modality. Therefore, this study seeks not only to compare the forms of teaching, but also to understand how these approaches impact on the acquisition of knowledge and the development of leadership skills. The results could contribute to future research and educational disciplines, enabling adaptations that combine the advantages of both modalities.

Among the possible limitations of the study, it is highlighted that as it is a specific population, the sample may undergo changes due to students withdrawing from participation in the collection period, making it necessary to recalculate the sample.

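### Students who withdraw after randomisation are deleted from the sample, which leaves the between-arm comparison open to bias of unknown direction and size

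*Protocol article*

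**What the plan says.** Management of losses or withdrawals promises that losses will be recorded and then fixes what happens to them: "If any participant withdraws from the study, they will be removed from the sample". It draws no distinction by timing, arm or reason, or by whether the student objects to use of data already given.

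The order of events is set under Intervention: "Randomization will be conducted only with participants who complete the pre-test and meet the eligibility criteria". Students are then told by WhatsApp and email which group they are in. Data collection and management lets them end participation at any time.

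The arms ask for different things. For the control arm, Allocation says: "Participants in the control group will attend a conventional expository class, held in person at the Nursing Department"; the class is a single four-hour afternoon session. For the online arm it says: "Participants will have a period of five days to access and consume the module’s content, totaling 30 hours, from registration to completion". Intervention adds: "Participants will have flexibility in accessing the classes and will not be restricted by geographical location". Both arms have the same nominal 30-hour workload, and both are called to the in-person post-test.

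Two other places bear on the point. Selection criteria ends its list of exclusions with "events that address the topic of leadership and absentees will be excluded from the study", without saying what the student is absent from. The Discussion foresees that "the sample may undergo changes due to students withdrawing from participation in the collection period", and its only response is to redo the sample calculation.

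**The concern.** The primary outcome is a comparison between arms: the online module is hoped to do as well as the conventional class or better. Randomisation supports that comparison only while the analysed groups are the randomised groups. A rule that deletes anyone who withdraws turns it into a comparison of those who stayed.

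The article's own design makes unequal loss plausible. Students learn their arm before the teaching starts, and a fixed afternoon in a classroom is a different commitment from self-paced access over five days. If those who leave differ in outcome from those who stay, and do so differently by arm, the estimated difference is distorted. With about 20 students per arm, a handful of removals counts.

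This is a stated rule about who is analysed, not a detail left to an analysis plan.

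**Working it through.** The plan has no figure to reproduce. The sample of about 40 is one of convenience, with no stated power, SD, margin or dropout rate. The check is therefore first of sequence, then an illustration of size.

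**Sequence.**
1. Pre-test and eligibility check, then randomisation (Intervention).
2. Students are told their arm (Intervention). Recruitment says they will not know it, but a classroom session and an online module cannot be mistaken for each other.
3. Class or module, with withdrawal possible at any time (Data collection and management).
4. In-person post-test for both arms (Allocation, Intervention).
5. Anyone who withdrew at steps 2 to 4 is removed (Management of losses or withdrawals), although a pre-test score exists.

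No other section keeps these students in the analysis or compares losses by arm.

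**Size, under assumptions.** Take normally distributed scores. Let d be the proportion lost from an arm and ρ the correlation between the tendency to stay and the score. Removing the leavers shifts that arm's mean by

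shift = ρ × φ(z_d) / (1 − d), in SD units.

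For ρ = 1 (exactly the lowest scorers leave):
- d = 0.10: 0.195
- d = 0.20: 0.350
- d = 0.30: 0.497

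The bias in the between-arm difference is the shift in one arm minus the shift in the other:

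| Loss, arm A vs arm B | ρ = 0 | ρ = 0.3 | ρ = 0.5 |
|---|---|---|---|
| 10% vs 10%, or 20% vs 20% | 0 | 0 | 0 |
| 10% vs 0% | 0 | 0.058 | 0.097 |
| 20% vs 5% | 0 | 0.072 | 0.121 |
| 20% vs 0% | 0 | 0.105 | 0.175 |
| 30% vs 5% | 0 | 0.116 | 0.194 |

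The table is symmetric: arm A may be either arm. If better scorers leave, the sign reverses. The zeros in the first row also assume the same mechanism of loss in both arms.

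**Yardstick.** With 20 per arm (40 split equally, an assumption), the 95% confidence interval half-width for a difference in means is 1.96 × √(2/20) = 0.62 SD. The 20% vs 0% case at ρ = 0.3 to 0.5 is then 0.105/0.62 = 17% to 0.175/0.62 = 28% of the half-width. Under perfect selection it is 0.350/0.62 = 56%.

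**Precision.** At an assumed two-sided 5% level and 80% power, the detectable difference is 0.89 SD with 20 per arm and 0.94 SD with 20 against 16. The loss of precision is modest; the issue is selection.

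**The case against.** The strongest reply is that the rule is narrower than it may look, and much of this stands.

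- A reader might infer that a student who stops the module but would still sit the post-test is lost. The text does not say so. It covers withdrawal from the study, sets no completion threshold for the module, and under Allocation calls all participants in both arms to the post-test.
- A reader might take the exclusion of absentees as a second post-randomisation deletion that works differently in each arm. The word stands among the selection criteria, which are applied before randomisation, so absence from the pre-test is a natural and harmless reading. Pre-test completion is, however, already a separate condition for randomisation, so absence from the class or post-test remains a possible reading. This is an ambiguity to close, not evidence of bias.
- A reader might expect weaker online learners to drop out, so that deletion flatters the module. Nothing in the document supports that direction. The fixed class could equally lose more control students.
- The illustration uses post-test level, whereas the tests named under Data analysis are paired pre-post tests. For change scores, the bias depends on how leaving relates to change, and that relation is not known either.

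What the reply does not remove is the sentence itself. It deletes randomised students who know their arm, and recording losses in a logbook does not put them back.

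**Conclusion.** The point holds, in limited form. The withdrawal rule drops randomised students from a between-arm comparison, in a design where the arms' demands differ and allocation is known to the student. The comparison is open to bias; it is not shown to be biased. Bias is zero if leaving is unrelated to outcome, or if loss and its mechanism are the same in both arms.

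Under the assumptions above, moderate selection with 20% loss from one arm gives about 0.10 to 0.18 SD. That is smaller than the random error of about 0.6 SD but not negligible. The 0.35 SD figure needs exactly the lowest fifth of one arm to leave and nobody from the other, so it is an upper illustration and not an expectation.

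**What to change.** Replace the withdrawal sentence with wording such as: *All randomised students are analysed in the arm assigned, whatever they attended or completed. Data already collected are kept unless consent to use them is withdrawn. Students who miss the class or do not finish the module are still called to the post-test.* The last part only makes explicit what Allocation already provides.

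In addition:
- Report losses and their reasons by arm.
- Handle missing post-tests with a between-arm analysis adjusted for the pre-test, which every randomised student has, or with multiple imputation. With only the post-test missing, imputation from pre-test and arm adds little to the adjusted analysis, so either will serve. Both assume that loss is explained by pre-test and arm, so add a best-case and worst-case analysis that includes every randomised student.
- Keep completers as a secondary analysis.
- In Selection criteria, state that absentees are students absent from the pre-test, before randomisation, so that the term cannot later be used to exclude randomised students.

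The cost is protocol wording, one more analysis, and some dilution of the effect by non-adherent students. The post-test session is already planned. The article says the study is still preparing to recruit, so the change can be made before any post-test is lost.

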### Data analysis

The results analyzed will be related to the evaluation of the effectiveness of the online educational module in the acquisition of knowledge about Leadership among Nursing students, and this effectiveness will be measured by means of a pre-test and a post-test, using a problem situation instrument and the QUAPEEL questionnaire.

Therefore, in addition to the age and gender of the participants, the variables to be analyzed will include the responses of the control and experimental groups, obtained by applying the instrument containing the problem situation and the *QUAPEEL* questionnaire (S4).

The collected data will be stored and processed using Microsoft Office Excel, version 2020, and Statistical Package for the Social Sciences (SPSS), version 25.0. The analysis will include both descriptive and inferential statistics, with results presented in tables and figures.

Descriptive data treatment will involve analyzing relative and absolute frequencies, mean, standard deviation, and medians according to the normality of the variables. The normality of the data distribution will be checked using appropriate statistical tests, such as the Shapiro-Wilk test or the Kolmogorov-Smirnov test.

The answers will be analyzed using the content analysis technique and the use of a frequency scale, ranging from “Never” to “Always”, aims to measure the participants’ self-perception in relation to the frequency with which they apply leadership practices in their daily lives. This approach is essential for assessing not only the presence of such practices, but also the consistency with which they are used in different scenarios. Although the focus is on frequency, the interpretation of the data allows inferences to be made about the participants’ understanding and use of leadership practices, in line with the objectives of the study.

To analyze the pre-test and post-test conditions of the study in this protocol, the tests to be used will depend on the distribution of the data. If the data is normally distributed, the Student’s t-test for paired samples will be used to compare the means of the two moments and check for statistically significant differences.

On the other hand, if the data does not follow a normal distribution, the Wilcoxon test for paired samples will be used, which is a non-parametric test suitable for comparing the medians between the two moments. The aim of both tests is to assess whether the changes observed between the pre- and post-test are statistically significant.

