There are still challenges in implementing leadership teaching in the training of nurses 22 years after the promulgation of the Curricular Guidelines for the Undergraduate Nursing Course. This occurs due to the outdated use of teaching methodologies, the fragility of teaching related to the lack of updating of teachers regarding teaching leadership and educational methods which have roots in conventional and traditional education [6].

As a way of mitigating the deficiency in teaching regarding the subject and given the possibility of exploring what digital educational technologies can provide to the learning process, the paradigm of teacher-centered education is broken and begins to value the student, providing an education capable of promoting meaningful learning [7].

Considering the above, there is a need to evaluate the effect of an online educational module in comparison with a conventional expository class related to knowledge acquisition by Nursing students on the topic of Leadership.

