### Study design

This is a Randomized Controlled Study in which participants will be selected at random and the study will be conducted in a single-blind manner, with assessments before and after the intervention. To do so, participants will be divided into a Control Group, which consists of subjects whose performance in relation to a dependent variable is used as a parameter to evaluate behavior; and the Experimental Group is the group of participants who receive the intervention [10]. Participants in the Control Group will undergo a conventional class while the other participants in the Experimental Group will undergo an online educational module.

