### Primary outcome

It is hoped that by applying the problem situation instrument, the primary result of this study will be to demonstrate that the online educational module has an equal or greater effect on the acquisition of knowledge about leadership by nursing students, compared to the conventional classroom. This knowledge covers concepts related to team engagement, organizational culture, conflict management, feedback and the concept of leadership. To measure these variables, we used the QUAPEEL questionnaire, structured with objective and quantitative items that assess both conceptual and practical aspects.

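### The primary question compares two randomised arms, but the only tests of effect specified are paired pre-test/post-test tests, and no between-arm test or estimate is given

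*Protocol article*

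**What the plan says.** The Introduction gives the objective as a need "to evaluate the effect of an online educational module in comparison with a conventional expository class". The Primary outcome section turns this into a directional hope: "the online educational module has an equal or greater effect on the acquisition of knowledge about leadership by nursing students, compared to the conventional classroom". Both statements are about a difference between the two randomised groups.

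The Data analysis section then fixes the tests. If the data are normal, it plans Student's "t-test for paired samples will be used to compare the means of the two moments and check for statistically significant differences". If they are not, "the Wilcoxon test for paired samples will be used, which is a non-parametric test suitable for comparing the medians between the two moments". It also states what the tests are for: "The aim of both tests is to assess whether the changes observed between the pre- and post-test are statistically significant". The other tests named there, Shapiro-Wilk and Kolmogorov-Smirnov, only check normality.

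The nearest the section comes to a group comparison is to list both groups' responses among the variables to be analysed and to promise descriptive and inferential statistics in general terms. No section names an independent-samples test, a model with a group term, an estimated difference between arms or an interval for it. The section also does not say whether the paired tests are run within each arm or on all students together.

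**The concern.** A paired test asks whether scores moved between two occasions. Here there are several reasons for them to move in both arms. Both groups are taught the same topics, both answer the same form twice, and both take it remotely the first time and in person the second (Allocation, Intervention, Data collection instrument). Teaching, retesting and the change of setting are mixed together in any pre-to-post change. Randomisation allows the shared part to be removed, but only through a contrast between arms.

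If the tests are run per arm, the natural temptation is to set one p-value beside the other. That is not a test of the difference and has no controlled error rate. If they are run on the pooled sample, group does not enter the analysis at all. Either way, a statement that the module is better than, worse than or similar to the class would have no inferential basis in the analysis specified.

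**Working it through.** **Question against test.** The documents give no power, alpha or effect size, so there is no planned figure to reproduce. The first check is to set the sections side by side.

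| Place in the protocol article | Contrast |
|---|---|
| Introduction, objective | online v conventional |
| Primary outcome | online v conventional, at least as good |
| Data analysis, normal data | pre v post, paired |
| Data analysis, non-normal data | pre v post, paired |
| Data analysis, stated aim of both tests | pre-to-post change |

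The mismatch is complete on either branch of the normality rule and needs no arithmetic.

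**Illustration of size.**

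From the documents: about 40 students (Study population), divided equally (Allocation), so 40 / 2 = 20 per arm.

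Assumed, because the documents give nothing: two-sided alpha 0.05; score SD 1; pre-post correlation r = 0.5; the true gains below; paired tests run per arm; normal scores. With r = 0.5 the SD of the change is sqrt(2 × (1 − 0.5)) = 1, so a gain in SD units equals the standardised gain.

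*Equal true gains in both arms.* If each paired t-test has power p, the chance that exactly one arm is significant is 2p(1 − p).

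| Standardised gain | p at n = 20 | Exactly one arm significant |
|---|---|---|
| 0.5 | 0.565 | 2 × 0.565 × 0.435 = 0.49 |
| 0.6 | 0.721 | 2 × 0.721 × 0.279 = 0.40 |
| 0.8 | 0.924 | 2 × 0.924 × 0.076 = 0.14 |
| 1.0 | 0.989 | 2 × 0.989 × 0.011 = 0.02 |

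Simulation with 40,000 runs agrees at 0.5, 0.8 and 1.0 (48.9%, 14.1%, 2.3%). In the same runs a direct between-arm t-test on change scores rejects in about 5%, as it should.

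*Online truly worse by 0.5 SD (gain 0.8 v 1.3).* Both paired tests are significant in about 92% of simulated trials. The control-arm test almost always succeeds at a gain of 1.3, so the joint figure is essentially the online arm's power at 0.8 (0.924). Two significant arms would invite a reading of equal benefit when the module is inferior.

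*Pooled version.* With gains of 0.8 v 1.6, a paired test on all 40 students is significant in essentially 100% of runs. It says nothing about which arm did better.

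**What a between-arm analysis would deliver.** For ANCOVA on the pre-test with r = 0.5, the residual SD is sqrt(1 − 0.25) = 0.866 and the standard error of the difference is 0.866 × sqrt(2/20) = 0.274 SD.

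- Power for a true difference of 0.5 SD: Phi(0.5/0.274 − 1.96), about 45%. Simulation gives 42% to 43%, with error of about 5% under equal gains.
- Approximate 95% CI half-width: 1.96 × 0.274 = 0.54 SD.
- Non-inferiority with an assumed margin of 0.5 SD (one-sided 0.025, 80% power, no true difference): 2 × (1.96 + 0.84)² × 0.75 / 0.25 = 47 before rounding of the quantiles and rounding up, so 48 per arm against about 20 available.

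The right analysis therefore answers the question with honest but wide uncertainty. A non-significant result could not be taken as equality.

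**The case against.** The strongest reply is that this is a condensed article. It promises inferential statistics, lists both groups' responses as variables, and introduces the paired tests as the way to analyse the pre-test and post-test conditions. It does not say that no other test will be run, and a fuller plan may contain a between-arm analysis. Part of this stands. A reader might infer that the team has decided never to compare the arms, and the article does not support that. It does not excuse the text, however. The article is not silent: it fixes the tests, the rule for choosing between them and their purpose, and these do not match its own primary comparison.

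A second reply is that the error rates above describe a misuse the article does not prescribe. That is correct. The article states no rule such as concluding for the module when only one arm is significant, and it does not say that the tests are per arm. The percentages also depend heavily on the assumed gain; discordance falls to about 2% at a gain of 1.0. They show what could go wrong and are not the plan's operating characteristics.

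A reader might also infer that a short, discrete score will nearly always fail a normality test, so that the plan amounts in practice to two Wilcoxon tests. The documents do not support this. The paired t-test assumption concerns the differences, and for differences of 0–4 or 0–6 scores at n = 20, Shapiro-Wilk rejected in only about 20% to just under 50% of simulated samples under assumed item probabilities. The number of items is itself unclear, QUAPEEL is scored 0 to 100, and the article does not say whether raw scores or differences are checked. The point needs none of this, because both branches are pre-post tests.

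**Conclusion.** The concern holds in this form: the only tests of effect that the article specifies are paired comparisons over time, while its objective and primary outcome are comparisons between arms, and no between-arm test or estimate is specified. This rests on the text alone and not on any assumed value. It must be corrected before the analysis, because the specified tests can neither support nor refute that the module is at least as effective as the class.

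The illustrative size is 49% to 14% one-arm-only significance under equal gains of 0.5 to 0.8, and about 92% double significance when online is worse by 0.5 SD. It depends on 20 per arm, assumed gains, a correlation of 0.5 and per-arm testing.

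**What to change.** In the Data analysis section, make the primary analysis a between-arm comparison: post-test problem-situation score regressed on randomised group with the pre-test score as covariate (ANCOVA), reporting the adjusted difference with its 95% CI. Fix this model in advance instead of letting a normality test choose, and add a permutation or rank-based between-arm check because the score is discrete. An independent-samples comparison of change would also cure the mismatch; ANCOVA is preferred for its precision. Keep the paired within-arm changes as descriptive only.

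Add a sentence saying that a non-significant difference will not be read as equality, and that any claim of equality or non-inferiority will be judged from the CI against a margin fixed in advance. The margin should be justified on educational grounds and set before data are seen. The text should acknowledge that about 20 per arm may be too few to meet it.

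The ANCOVA change costs only wording: the pre-test is already collected, SPSS is already named and fits the model, and the Study situation section describes the trial as still preparing for recruitment. Choosing a margin needs a substantive decision by the investigators, and the registry entry should be updated to match.
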